### Data management and monitoring

All data collected by the research team will be collected by means of the unique number assigned to each participant and entered at the data collection site. All data and personal information present on questionnaires and data sheets will be anonymize. In order to ensure the security of personal information and data, we will use security procedures such as encryption and password protection as a standard practice. Personal information and data collected will only be handled by the Principal Investigator and project coordinator, who will anonymize the data for data analyses by collaborators.

The Principal Investigator, the project coordinator, and an independent researcher who will not be involved in the trial will comprise the Data Monitoring Committee (DMC). On a monthly basis the DMC, which is independent from the sponsors and competing interests, will meet for data control and quality and ensure its validity. In case of aberrant outcomes and/or missing data, the DMC will contact the pertinent participant and researchers.

### Statistical analysis

Outcome analysis will be performed blinded to group allocation. The descriptive analysis of the sample will be expressed as mean and standard deviation for continuous and normally distributed variables, meanwhile non-normal distributed variables will be presented as median and interquartile range. Categorical variables will be presented as number and percentage with their standard error. Normality and homogeneity will be tested by using Kolmogorov-Smirnov test and Levene’s test, respectively. When necessary, appropriate transformations will be applied in case of non-normal distributions.

The analysis of the data set will follow an intention-to-treat design and all randomized participants for whom baseline assessments were conducted will be included in the final analysis.

To analyze the outcomes of the study we will use linear mixed-effect models with repeated measures. We will assess changes over time (W -1; W 24; W 48) and between study arms. Appropriate post-hoc tests will be implemented to analyze within and between group differences of the study arms at each time point. Categorical variables will be analyzed using Pearson’s χ-squared or Fisher’s exact test at baseline, after intervention and follow-up period.

To examine the correlations between the different outcomes, Pearson’s correlations and multiple regression analysis will be performed.

If necessary, baseline differences between the trial arms on outcomes variables will be used as covariates and fitted as factors in the models.

Two-sided tests of statistical significance will be used in all analyses. Effects size of the interventions will be presented in addition to significance tests. Significance levels will be set at an alpha level less than 5%. Statistical analyses will be conducted using SPSS v. 25 (IBM SPSS Statistics, Chicago, IL, USA).

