**Methods:**

In this trial, ninety seniors with ID between the ages of 40 and 75 yrs. from occupational health centers from the Autonomous Region of Catalonia (Spain) will be recruited. Participants will be randomly allocated to the CAEP, SIT, and control group. Both intervention groups will train 3 days/week, 1.5 h/day over 6 months. Outcome variables will be assessed at baseline, 6 months and 12 months. The outcome variables include weight, height, body composition, cardiorespiratory fitness, muscle strength, balance, flexibility, cardiovascular parameters (blood pressure, pulse-wave velocity, pulse-wave analysis), QoL and cognitive function. The intervention effect will be determined with mixed models with repeated measures to assess changes in the outcome variables over time (baseline to month 12) and between study arms. Relationship between variables will be analyzed with appropriate regression analyses.

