## Methods

### Study aims

The present trial aims to evaluate and compare the effectiveness of two different 6-months exercise programs on the health-related fitness of seniors with ID. Secondary to the main objective, this study will compare the effects of these interventions on the blood pressure, arterial stiffness, pulse wave velocity, PA levels and sedentary behaviors of the participants. Lastly, we seek to investigate the effect of the exercise programs on the QoL, emotional and cognitive function of the volunteers.

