### Study design

The present study protocol describes a longitudinal three-armed parallel-group randomized controlled trial to evaluate and compare the effectiveness of two different multi-component exercise programs for seniors with ID.

A total of 90 participants from occupational day centers from Catalonia (Spain) will be recruited and randomly allocated to the CAEP, or SIT program or control group (CG). Participants from both exercise groups will receive a 24-week supervised exercise program, 3 times/week, 90 min/session. Participants from the CG will be visited by the researchers once a week to observe if they maintain their usual lifestyle. Outcome variables will be assessed at baseline (W − 1), month 6 (W 24; end of intervention) and month 12 (W 48; 6 months follow-up). After month 12, the CG will receive the SIT intervention in order to experience similar exercise-related health-benefits.

This study was approved by the Institutional Review Board (CER URL 2017_2018_008) and complies with the principles of the Declaration of Helsinki [37]. The trial is registered as a current randomized controlled trial (registration number: ISRCTN43594228; registration date: 11 February 2019). Figure 1 presents the participant flow for this trial. The present protocol follows the Standard Protocol Items Recommendations for Interventional Trials (SPIRIT) guidelines and fulfills the SPIRIT checklist.

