## Discussion

To counteract the high prevalence of cardiovascular risk factors, decreased physical fitness [70–72], premature aging [11, 73], and overcome different barriers that seniors with ID have to face to live and active life [9, 74], it is essential to design exercise programs that best suit their needs. Therefore, the main objective of this study is to design two specific PA programs for seniors with ID and determine which of them will generate the greatest benefits in health-related physical fitness, cardiovascular parameters, QoL and emotional and cognitive aspects.

This study will span 12 months. After 6 months, participants will be followed up for 6 months without training. Finally, 12 months after starting the study, all participants in the CG will be offered the possibility to participate in the SIT program for 6 months.

Previously, numerous multi-component programs implemented continuous aerobic training in adolescents [22, 75], adults [24–26, 76, 77] and seniors with ID [21, 23, 78]. Also, some studies implemented SIT programs for adolescents and young adults with ID [31] and with Down syndrome [32]. Nevertheless, none of these studies implemented SIT programs specifically designed for seniors with ID. Furthermore, the present study will try to elucidate if exercise interventions promote beneficial changes on cardiovascular measures of central and peripheral arteries and which of these programs will have the most significant effect on the outcome variables.

Given the direct associations between cardiorespiratory fitness and mortality [79], muscular fitness and mortality [80], and the important effects of high intensity interval training programs on muscular adaptation and remodeling [81], it is necessary to further investigate the effects of SIT programs on overall fitness and vascular function in seniors with ID.

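### The protocol names no primary contrast or visit, plans within-arm and visit-by-visit tests including baseline, and makes baseline adjustment optional, although the aim is to say which programme works better

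*Protocol article*

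**What the plan says.** The design is a "longitudinal three-armed parallel-group randomized controlled trial to evaluate and compare the effectiveness of two different multi-component exercise programs" (Study design), with arms CAEP, SIT and control. The aim reads: "The present trial aims to evaluate and compare the effectiveness of two different 6-months exercise programs on the health-related fitness of seniors with ID" (Study aims). The Discussion restates the objective as to "determine which of them will generate the greatest benefits in health-related physical fitness", along with other domains.

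The Statistical analysis section plans linear mixed models with repeated measures: "We will assess changes over time (W -1; W 24; W 48) and between study arms". It continues: "Appropriate post-hoc tests will be implemented to analyze within and between group differences of the study arms at each time point". It also says "Two-sided tests of statistical significance will be used in all analyses" and sets alpha below 5%. Baseline imbalances on outcome variables enter the models as covariates only where this is judged necessary.

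The primary outcome is maximal aerobic capacity, measured as VO2 peak in both L/min and ml/kg/min (Primary outcome measurement). The sample size uses a 0.2 L/min increase with an SD of 0.1 L/min, but does not say which arm comparison or visit this belongs to (Sample size). Nowhere does the article rank SIT against CAEP, SIT against control and CAEP against control, or choose between week 24 and week 48.

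**The concern.** With three arms and three visits, the planned follow-up tests cover 3 arm pairs × 3 visits = 9 between-arm comparisons and 3 arms × 3 visit pairs = 9 within-arm comparisons for VO2 peak on one scale. The plan does not say which of these answers the trial's question.

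Three features pull away from that question:

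- A within-arm test asks whether one arm changed over time. It does not compare programmes.
- Three of the nine between-arm comparisons are at baseline. After randomisation any difference there is due to chance, so the test informs nothing.
- A between-arm difference in raw level at a later visit ignores each person's starting value. Adjustment that depends on the imbalance seen leaves both the estimator and its precision to be settled after the data are in.

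At stake is whether the trial can state one pre-specified answer to which programme is better, and how much power it has for that answer.

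**Working it through.** **The plan's own sample size.** The dropout step reproduces: 24 / (1 − 0.20) = 30 per arm, 90 in total. The 24 does not follow from the stated inputs: 2 × (1.960 + 0.842)² × (0.1/0.2)² = 3.9, so 4 per arm by the normal approximation for two means. Working back, 24 per arm corresponds to an SD of about 0.247 L/min. That is a separate matter. It bears on this point only because the article gives no dependable cross-sectional SD, so a range is assumed below.

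**Power for a between-arm difference at week 24.** Inputs from the Sample size section: difference 0.2 L/min, 24 completers per arm, two-sided 5%. Assumed, not in the article: SD of VO2 peak at one visit σ = 0.3 to 0.5 L/min, and correlation between baseline and week 24 ρ = 0.7. The test is a two-sample t-test with 46 degrees of freedom and noncentrality 0.2 / (SD × √(2/24)).

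| Analysis | SD used | Noncentrality | Power |
|---|---|---|---|
| Raw level at week 24 | σ = 0.30 to 0.50 | 2.31 to 1.39 | 62% to 27% |
| Change from baseline | σ√(2(1 − ρ)) = 0.232 to 0.387 | 2.98 to 1.79 | 83% to 42% |
| Baseline-adjusted | σ√(1 − ρ²) = 0.214 to 0.357 | 3.23 to 1.94 | 89% to 48% |

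If 0.1 L/min really were the SD of a single measurement, noncentrality would be 0.2 / (0.1 × 0.2887) = 6.93. Power would then be essentially 100% even for the raw comparison, and the choice would hardly matter for power.

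**False-positive rates with no true difference between any arms.** Simulation of 40,000 trials, 24 per arm, pooled variance, each pair tested at two-sided 5%, with an assumed correlation of 0.6 between the two post-baseline visits:

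| Event | Week 24 | Week 24 or 48 |
|---|---|---|
| At least one of the 3 pairs, ungated and unadjusted | 12% | 20% |
| At least one pair, tested only after a significant three-arm test at that visit | 5% | 9% |
| SIT against CAEP alone, unadjusted | 5% | 9% |

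The first row counts false differences from control as well as between programmes. Only the last row measures the chance of wrongly declaring one programme better by direct comparison.

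**The case against.** The strongest reply is that the article condenses a fuller plan. The post-hoc tests are described only as appropriate, which could mean Tukey, Bonferroni or pairwise tests after an overall test. A missing multiplicity rule is detail that an article may leave to the analysis plan. That stands: the 12% and 20% are conditional on the ungated, unadjusted reading, and with a per-visit overall test they fall to 5% and 9%. The stated alpha ("Significance levels will be set at an alpha level less than 5" per cent) does not settle which reading applies.

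A second reply is that a mixed model including baseline can estimate change, so the raw comparison is not the only reading. That also stands. But the follow-up tests are defined as differences at each visit, and baseline covariates are conditional, so the text does not commit to the efficient analysis.

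Two stronger readings are tempting and should not be drawn.

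- A reader might infer that a programme will be declared better because its within-arm change is significant and the other's is not. For two identical programmes, each with within-arm power p, that split occurs with probability 2p(1 − p): 50% at p = 0.5 and 32% at p = 0.8. But the article never says it will reason this way, and it plans direct between-arm tests. At its own assumed gain of 2 SD, the split has a probability near zero.
- A reader might take the abstract's phrase "assess changes in the outcome variables over time (baseline to month 12) and between study arms" to mean that the trained state and the untrained follow-up are merged into one effect. Study design and Outcome measurements keep week 24 and week 48 apart, and the Discussion separates the 6-month change from whether it is maintained. The phrase gives the span of measurement.

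Finally, powering on L/min suggests that this is the intended primary scale, so counting both scales as co-primary would overstate the number of tests.

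**Conclusion.** The concern holds in a limited form. The protocol aims to say which programme works better but names no primary contrast or visit, plans within-arm and baseline tests that cannot answer the question, and leaves baseline adjustment to observed imbalance.

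The firmest cost is efficiency: 62% to 27% power for a raw week 24 comparison against 89% to 48% with adjustment. This rests on an assumed SD of 0.3 to 0.5 L/min, a correlation of 0.7 and 24 completers per arm. The gain is smaller against an analysis of change (83% to 42%), and it disappears if the SD is as small as 0.1 L/min.

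The error-rate cost is conditional. It is about 12% at week 24 and 20% over both follow-up visits for any false pair if tests are ungated and unadjusted, and about 5% and 9% for a false direct SIT-CAEP difference. The documents do not show that the trial will name a better programme from within-arm p-values. The defect is that no rule says which result will carry the conclusion.

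**What to change.** Amend the Statistical analysis section, before any unblinded analysis, as follows:

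- Primary analysis: between-arm difference in VO2 peak (L/min) at week 24 from the mixed model, always adjusted for baseline VO2 peak whatever imbalance is seen.
- Contrasts: SIT against control, CAEP against control and SIT against CAEP, either in a stated order or with a multiplicity adjustment such as Holm. State that only the direct SIT-CAEP contrast can support naming a better programme.
- Secondary: week 48, VO2 peak in ml/kg/min, and the remaining outcomes.
- Drop tests of baseline differences. Report within-arm changes as estimates with confidence intervals.

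No data collection changes. The cost is some power per contrast. Under the assumptions above, Holm's strictest step for three contrasts (0.05/3 = 0.0167) lowers adjusted power from 89% to 77% at SD 0.3 and from 48% to 30% at SD 0.5, still above the raw unadjusted comparison (62% and 27%). Later Holm steps lose less. A fixed order spares the first contrast any loss, but a later contrast can then be tested only if those before it succeed.

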### Sample size

An average increase in VO_2_ peak of 0.2 L/min was reported in previous studies that implemented multi-component exercise programs for adults with ID [26, 32]. In the present study, a target increase of 0.2 L/min and a standard deviation of 0.1 L/min in VO_2_ peak has been used for sample size calculation [38]. Assuming a 95% confidence level, 5% alpha error, and 20% beta error, with a 1:1:1 ratio between groups, we will seek to recruit 24 participants per group. To allow for a drop-out rate of 20% throughout the study, a total of 90 participants, 30 participants in each group, will be required.

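### Baseline is adjusted for only if an imbalance is seen, in a model where W -1 is already a response; pre-specify it for every continuous outcome to recover precision

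*Protocol article*

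**What the plan says.** All of this is in the protocol article, Statistical analysis. The model is stated as "To analyze the outcomes of the study we will use linear mixed-effect models with repeated measures". Its time levels follow: "We will assess changes over time (W -1; W 24; W 48) and between study arms". Read plainly, the baseline visit W -1 is one of three response levels.

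Arms are then compared visit by visit: "Appropriate post-hoc tests will be implemented to analyze within and between group differences of the study arms at each time point". Near the end of the section comes the adjustment rule: "If necessary, baseline differences between the trial arms on outcomes variables will be used as covariates and fitted as factors in the models".

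The same section says the analysis follows intention to treat and includes everyone randomised who had a baseline assessment. Under Randomization and blinding, the strata are level of ID, Down syndrome and sex. Baseline VO2 peak, the primary outcome's own baseline, is not balanced by design.

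**The concern.** There are two problems.

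- **The rule is driven by the data.** Whether baseline enters depends on the observed imbalance, and the article says nothing about how much imbalance is enough. The covariate set can therefore differ between outcomes. With many secondary outcomes some chance imbalance is certain: at an assumed trigger of p<0.05, about one outcome in 20.
- **Covariate and response can be the same number.** If W -1 is a response and the same outcome's baseline is added as a covariate, the adjustment does not act as it would in an ANCOVA of follow-up values.

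At stake are the precision of the primary comparison and, in analyses where the covariate is switched on, the calibration of the W 24 test.

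**Working it through.** **Inputs.** From the documents: three visits; two-sided 5% tests; three arms with "5% alpha error, and 20% beta error, with a 1:1:1 ratio between groups, we will seek to recruit 24 participants per group". The drop-out step reproduces: 24/(1 − 0.20) = 30 per arm, 90 in total. The documents give no type I error for the adjusted model, so there is no figure of the plan's own to reproduce.

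Assumed, because the documents do not give them: the correlation ρ between visits (range 0.3 to 0.9), variance 1 at each visit, a random-intercept model, and a trigger of baseline p<0.05.

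**1. Change contrast.** A main-effect term β × baseline is the same at every visit of a participant. It cancels from any within-person difference in complete data. In a fitted example (ρ = 0.7, 24 per arm) the arm-by-time contrast, W -1 against W 24, was −0.164 with SE 0.222 both with and without the covariate. The W 24 arm difference in the same data moved from 0.366 (SE 0.270) to 0.199 (SE 0.179).

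**2. W 24 comparison when the covariate is in the model, equal correlations.**
- Fitted slope: β = (1 + 2ρ)/3. At ρ = 0.7, β = 2.4/3 = 0.80, above the correct slope of 0.7.
- True variance of the adjusted value: 1 + β² − 2βρ = 1 + 0.64 − 1.12 = 0.52.
- Variance the model assumes: 1 − β² = 0.36.
- Type I error: 2[1 − Φ(1.96 × √(0.36/0.52))] = 2[1 − Φ(1.631)] = 10.3%.

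| ρ | β | true variance | model variance | type I error |
|---|---|---|---|---|
| 0.3 | 0.533 | 0.964 | 0.716 | 9.1% |
| 0.5 | 0.667 | 0.778 | 0.556 | 9.8% |
| 0.7 | 0.800 | 0.520 | 0.360 | 10.3% |
| 0.9 | 0.933 | 0.191 | 0.129 | 10.8% |

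Simulation of 40,000 null trials per setting agrees (9.3% to 10.8%). With correlations that decay over time (0.7 then 0.49, or 0.85 then 0.72) and the same model, the figures are 6.4% and 5.7%.

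**3. The rule as written.** With the p<0.05 trigger, overall type I error of the W 24 test was 2.7% to 5.3% over ρ = 0.3 to 0.9. At ρ = 0.7, 24 per arm, with the trigger firing in about 5% of trials: 0.05 × 0.129 + 0.95 × 0.034 = 3.9%.

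**4. Triggered trials only, equal correlations.** The adjusted W 24 test rejected in 10% to 13%. The unadjusted W 24 test in those same trials rejected in about 10% at ρ = 0.3, 19% at 0.5, 35% at 0.7 and 60% at 0.9 (24 per arm).

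**5. Precision forgone.** Per-person variance is 2(1 − ρ) for the change score and 1 − ρ² for ANCOVA with baseline always in. The ratio is (1 + ρ)/2.
- ρ = 0.5: 0.75/1.00 = 0.75, a 25% saving.
- ρ = 0.7: 0.51/0.60 = 0.85, a 15% saving.
- ρ = 0.9: 0.19/0.20 = 0.95, a 5% saving.

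Against the unadjusted W 24 comparison (variance 1) the ANCOVA variance is 1 − ρ², a saving of ρ²: 25% at 0.5 and 49% at 0.7. ANCOVA of W 24 held its type I error at about 5% (4.8% to 5.1%) under equal correlations.

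**The case against.** A reader might infer that the plan doubles the type I error. The documents do not support that. The 10% figure needs the covariate to be in the model, a random-intercept structure and roughly equal correlations, and the article fixes none of these. Applied conditionally, the rule keeps the overall error near or below 5%. In triggered trials the unadjusted W 24 test is no better at ρ = 0.5 and above, and often far worse. So the case is for always adjusting in a sound way, not for never adjusting.

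A reader might also infer that the adjustment can never help the change contrast. That holds only for complete data and a main-effect covariate, and the plan expects 20% drop-out. A baseline-by-time term would make the change contrast ANCOVA-like. It would not repair the W 24 test under the same random-intercept model. Baseline residuals are then zero, the pooled variance is 2(1 − ρ²)/3 against a true 1 − ρ², and the error is 2[1 − Φ(1.96 × √(2/3))] ≈ 11%. With an unstructured covariance the model degenerates, since a slope of 1 leaves no residual variance at W -1.

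Three further points stand in part:
- The sentence could refer to baseline values of other outcomes, where the double use does not arise. The dependence on observed imbalance remains either way.
- Fitting baseline as a factor is probably loose wording, since the same sentence calls it a covariate. Nothing says a continuous baseline will be categorised.
- Covariance structure and covariate-by-time terms may properly sit in an analysis plan that is not shown, so their absence is not criticised here. What is criticised is the conditional rule that the article does state.

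Finally, the unadjusted change and W 24 analyses are valid: both held about 5% in simulation with equal correlations.

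**Conclusion.** The point holds as a should-fix. The article states an adjustment rule that depends on observed imbalance, has no criterion, and sits in a model where W -1 is already a response. There, adding the outcome's own baseline as a main effect does nothing for the change contrast in complete data. It can miscalibrate the W 24 test in the analyses where it is used: about 10% with a random intercept and equal correlations, about 6% with decaying correlations.

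Overall type I error under the rule, with an assumed p<0.05 trigger, is 2.7% to 5.3%, so this is not a general validity failure. The main cost is precision: 5% to 25% of the variance of the change contrast for ρ from 0.9 down to 0.5. Every size here rests on an assumed ρ.

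**What to change.** Delete the conditional sentence and pre-specify how baseline is handled for every continuous outcome, whatever imbalance is observed.

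- **Preferred:** keep W -1, W 24 and W 48 as responses and constrain the arm means to be equal at baseline. Every randomised participant with a baseline stays in the model, which matches the article's own intention-to-treat statement.
- **Alternative:** fit W 24 and W 48 only, with the outcome's baseline as a continuous covariate, baseline-by-visit, arm, visit and arm-by-visit. The small downside is that participants with no follow-up value drop out of this model, which does not sit well with that statement.

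Either way the cost is a change of analysis wording. The baseline measurements are already in the assessment schedule, and no visit, test or participant is added.
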